## Abstract

**Background:**

In India, approximately 3.5 million children are affected by Developmental Delay (DD), often stemming from preterm births. These delays contribute to neurological and motor development delays, placing a significant financial burden on families. Maternal unemployment rates are also elevated in such cases. Delayed Developmental Milestones identification, often due to a lack of parental awareness, further compounds these challenges. This study introduces a multiphasic approach aimed at educating antenatal women on monitoring neurological maturation, with the overarching objective of assessing the effectiveness of a targeted multi-method parental education intervention in improving parents’ knowledge and early detection of developmental disorders in early childhood.

**Methods:**

Antenatal women will be assigned to intervention or control groups. The intervention group will undergo specialized training in a multiphasic study, while the control group will receive routine care. A meticulously developed intervention module for early detection of neurodevelopmental disorders will empower mothers to monitor their newborns for potential deficits. Outcomes will be assessed through questionnaires, analyzing knowledge improvement and early identification of DD using statistical methods such as chi-square tests. The study involves three phases: preparatory, implementation, and evaluation, aiming to empower mothers to detect developmental concerns early and improve maternal awareness of child development. The study was approved by the SRM Institutional Ethical Committee with the reference number 8688/IEC/2023.

**Discussion:**

This study will identify DD and improve parental awareness by providing tools for early detection thereby empowers parents to identify developmental concerns early. The study supports policy goals to reduce the burden of DD, enhance early intervention, and improve long-term outcomes for children. It is anticipated that this intervention will complement existing health policies, contributing to better child health and developmental outcomes in India.

**Trial registration:**

Trail is registered under Clinical Trails Registry - India (CTRI/2024/04/065008) registered on 01 April 2024.

**Table Taba:** 

Text box 1. Contributions to the literature
• The utilization of multiphasic approaches such as scoping reviews, interviews, expert validation, co-designing, and pilot testing in the development of checklist and antenatal educational module enables iterative refinement.
• Educating mother right from the antenatal period about the red-flags in developments, helps increasing the rate of early screening and referral thereby mitigating the long term complications.
• In contrast to the common practice of adapting tools from a single established source, this research aims to develop a comprehensive tool that combines elements from multiple validated tools. This integrative approach ensures both methodological rigor and structural reliability.

## Background

Early childhood is a critical period for a child’s development. Developmental delays, if undetected and untreated, can have significant long-term consequences [1]. Developmental Delay (DD) pose a significant global health challenge, particularly affecting children in developing countries [2]. In South Asia, a staggering 53 million children under five are diagnosed with DD, with India bearing the brunt of this burden [3–5]. Globally, an estimated 180–200 million children under five experience developmental delays [6]. In India alone, at least 10% of young children are affected [7]. 

Preterm birth is one of the major contributors to neurodevelopmental disorders (NDDs) globally and in India. Studies indicate that one in two surviving preterm infants develops NDDs by the age of two. India contributes significantly to the global burden of preterm births, accounting for 23.4% of the total [8–11]. Premature infants often suffer from neurological impairments, such as incomplete myelination and immature brain development, which can lead to long-term developmental delays affecting their motor and cognitive abilities [12, 13]. Compounding this issue, factors like poverty, malnutrition, and limited access to healthcare further elevate the risk of DD [14]. Beyond the individual influence, DD have far-reaching consequences which impact multiple Sustainable Development Goals, including poverty, hunger, health, education, economic growth, and inequality [15]. Families of children with DD often face significant economic burdens, with 10% of mothers are forced to quit their jobs to care for their children [16]. In addition, socioeconomic factors such as poverty, malnutrition, and limited access to healthcare exacerbate the risk of DD [17].

Early identification of these delays is crucial for timely intervention and optimal outcomes [18, 19]. Parental awareness plays a key role in early detection, as parents are often the first to notice developmental deviations in their children [20]. However, a significant gap in maternal knowledge and awareness about developmental milestones and red flags persists, especially in rural and underserved regions in India, where access to healthcare resources is limited [21]. This lack of awareness will hinder the early identification and delay necessary interventions [22].

To address this pressing issue, it is crucial to empower mothers with the knowledge and skills to recognize early signs of developmental delays. Recognizing primitive reflexes and their persistence becomes a crucial diagnostic and prognostic factor for DD, especially during the pivotal 0–3 years when neurological maturity is at its peak [23–25]. Targeted parental education interventions provide a promising approach to empower parents to recognize developmental delays and seek timely treatment services [26]. By equipping parents with accurate information and practical tools, these interventions aim to enhance parental awareness, improve early identification rates, and ultimately optimize child development. By providing maternal education during the antenatal and postnatal periods, we can facilitate early diagnosis, prompt intervention, and ultimately improve the lives of children with DD [27, 28].

By implementing this strategy, we aim to facilitate early diagnosis, prompt specialized care, and improve long-term outcomes for children with developmental delays [29]. This will contribute to a brighter future where inclusion and healthy child development are prioritized [29]. Therefore, this study aims to evaluate the effectiveness of a targeted parental education intervention in improving parental awareness and early identification of developmental delays.

## Methods

### Research question

Will targeted parental education during the antenatal period about red flag signs in developmental milestones from 0 to 1 year improve early detection of childhood developmental disorders?

## Hypothesis

Mothers in the Intervention group can identify the early red flag signs of developmental disorders more easily than the control group.

### Study objectives

#### Primary objectives

To develop targeted multi-method parental education intervention on the detection of early red flag signs of early childhood developmental disorders.To determine the effect of targeted multimethod parental education intervention on the identification of suspected early childhood developmental disorders by the parents.

#### Secondary objectives

To determine the yield of early detection by parents of early red flag signs of childhood developmental disorders.To estimate the level of improvement of knowledge in early red flag signs of childhood development disorders among the parents.

### Methodology

This non randomized interventional study will be carried out among Antenatal mothers from 2nd Trimester of pregnancy at SRM Medical College Hospital, Research Centre, other established centres in Chennai and Trichy and Tanjavur Medical College, Tanjavur, Tamil Nadu, India. The study was approved by the Institutional Ethical Committee with the reference number 8688/IEC/2023 and was accepted by Indian Council of Medical Research (ICMR), a peer reviewed funding agency after reviewing for the methodological soundness. (Proposal id IIRP-2023-7817/F1). Trial has been registered under Clinical Trials Registry (CTRI/2024/04/065008).

### Eligibility criteria

For the intervention group, eligible participants include antenatal mothers who have provided informed consent and are willing to participate in the neuro-parenting program. These participants will need to be available for follow-up assessments at specified intervals to evaluate the intervention’s impact on early childhood development awareness. The control group will comprise antenatal mothers who are receiving routine antenatal and postnatal care without access to the neuro-parenting intervention; they will also provide informed consent and commit to follow-up visits. Exclusion criteria for both groups will include any mothers with medical conditions that could independently influence neurodevelopmental outcomes, as well as those who may face challenges in completing the follow-up.

**The study will be conducted in three phases namely**,

Preparatory Phase.Implementation Phase.Evaluation Phase.

#### Preparatory Phase

This phase will be a meticulous and iterative process, ensuring the development of a well-validated tool for assessing early indicators of neurodevelopmental disorders in infants which in turn, facilitates the effective monitoring and intervention strategies through parental education. Information on neurodevelopmental sequence, posture, milestones, reflexes will serve as the foundation for the material development. The following steps will be involved in this phase.

**Desk Review**: A comprehensive review of existing literature, encompassing both published and grey literature for identifying validated tools used to assess neuromotor maturity, neurodevelopmental outcomes, and indicators of neurodevelopmental disorders in infants.**Expert Review**: Components will be gathered from the identified tools and will be charted according domains for each quarter of infant’s life. A panel discussion with domain experts, including paediatricians, neonatologists, physiotherapists, occupational therapists, speech language pathologists, developmental pediatricians, obstetricians, and gynaecologists will be conducted. Their valuable insights will guide the creation of a pilot version of the tool, incorporating critical assessment aspects and early indicators of developmental disorders detectable within the first year of life.**Stakeholder Engagement**: Focus group discussions will be conducted among antenatal mothers, family members, community health workers and NICU staff nurses and efforts will be made to align the module standards with the local population’s knowledge level. Delphi rounds will be conducted to analyse the feasibility for the component to be taught to the mother and is safe for mother to assess. A co-design approach will be employed for the development of the tool. It also assesses module relevance, comprehensibility, and practicality, which will result in the refinement of the tool’s content.**Pilot-testing**: The developed tool will be tested with a subset of targeted participants, which will provide valuable insights into practical challenges and real-world application. The outcomes will inform the feasibility of the tool and its alignment with the intended objectives.**Enhancement of the Tool**: A feedback consultation with aforementioned stakeholders will cover various aspects, including implementation strategy, benefits, barriers, cost, comprehensibility, feasibility, and success rate. Collaborative adjustments, language and sociocultural adaptations for the refinement of the tool that will be comprehensible by any antenatal women or mother. The checklist will focus on all developmental domains, including primitive reflex, tone, fine motor skills, gross motor skills, cognitive, and social development.**Formalization of the tool into an antenatal training module**: The refined material will be crafted to educate stakeholders on essential developmental concepts, emphasizing the significance of the first year of life, critical monitoring periods, checklist item explanations, assessment documentation, and interpretation. Antenatal counselling strategies are also included to alleviate parental stress.

A curriculum model will be developed for maternal education incorporating adult learning methods. Multimethod of teaching including video demonstration, in person teaching and Training of Trainers printed material-based teaching will be implemented.

Simultaneously, a thorough desk review is conducted to evaluate existing materials and videos aimed at enhancing mothers’ knowledge of early child development. Validity measures, including content validity, face validity, and construct validity, will be employed to ensure the robustness of the tool.

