##### Sample size & sampling methodology

Anticipating a 5% exposure rate to neuro parenting among multigravida women during the study period and aiming for an odds ratio (OR) of 2 with 80% power and 95% confidence interval (CI), with 20% drop out rate the sample size calculation involves recruiting 513 participants per group, rounded to the nearest number, resulting in a total of 520 participants in each arm.

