### Training and assessment

In this phase, all participants will undergo a thorough assessment of training outcomes. The implementation strategy involves providing participants with a comprehensive questionnaire covering knowledge, awareness, and practices related to identifying early child development delays based on the training module. This questionnaire will be administered after the completion of the training module. Upon concluding all training sessions, a final questionnaire will be developed to gauge participants’ overall knowledge, practice, and understanding of the training’s importance. Descriptive statistics will be calculated to analyse quantitative variables, providing insights into the numerical aspects of the participants’ responses. For quantitative variables, frequencies and percentages will be computed, offering a quantitative overview of the participants’ understanding and practices. To explore the association between variables, the chi-square test will be employed, with a significance level set at 5%.

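### The sample size and the only named test treat mothers as independent, although in-person and Training-of-Trainers teaching in the trained arm alone may correlate outcomes within trainer

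*Protocol article*

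**What the plan says.** - **Delivery.** The curriculum paragraph under Preparatory Phase names video demonstration and adds that "in person teaching and Training of Trainers printed material-based teaching will be implemented". The Intervention section describes an online module and three sessions: second trimester, third trimester and postnatal. The Implementation phase section says that controls have no training sessions.
- **Sites.** The Methodology section names one medical college hospital together with "other established centres in Chennai and Trichy and Tanjavur Medical College". It does not say how the two arms are spread over the sites.
- **Sample size.** The section Sample size & sampling methodology starts from "Anticipating a 5% exposure rate to neuro parenting among multigravida women during the study period". It continues "aiming for an odds ratio (OR) of 2 with 80% power and 95% confidence interval (CI"), with 20% dropout, and reports that "the sample size calculation involves recruiting 513 participants per group", rounded to 520 per arm. It mentions no design effect, ICC, number of trainers or number of centres.
- **Test.** Under Training and assessment, "the chi-square test will be employed, with a significance level set at 5" per cent. The Abstract also gives chi-square as an example of the methods for knowledge and early identification. No other test is named.

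**The concern.** A chi-square test and a two-proportion sample size both assume that one mother's outcome says nothing about another's. The primary outcome is whether a mother suspects a developmental disorder, split into true and false positives. How a trainer explains red flags could plausibly raise or lower that threshold for every mother taught by that trainer. Outcomes in the trained arm would then be correlated within trainer, with no counterpart among controls.

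At stake is the standard error. One or two unusually strong or weak trainers could move a whole block of the trained arm, and a plain chi-square would read that as evidence from many separate mothers. This is distinct from confounding in a non-randomised comparison and would remain if the arms were otherwise comparable. The power side is hard to repair later: an analysis plan can change the test, but it cannot restore information once recruitment has stopped at 520 per arm.

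**Working it through.** **Step 1. Reproduce 513.** Inputs from the sample size section: reference rate 5%, odds ratio 2, 80% power, 95% confidence (read as two-sided 5%), equal arms. The 5% is worded as an exposure rate and is used here as the control proportion.

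- Trained-arm proportion: p1 = 2 × 0.05 / (1 + 0.05) = 0.0952. Difference d = 0.0452.
- Binomial variances: 0.05 × 0.95 = 0.0475, and 0.0952 × 0.9048 = 0.0862.
- n = (1.960 + 0.842)² × (0.0475 + 0.0862) / d² = 512.7, so 513.

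This matches exactly with no inflation, so the design effect is 1. It also matches before any dropout allowance: 513 / 0.8 is about 642.

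**Step 2. Separate dropout from clustering.** If 20% of 520 are lost, 520 × 0.8 = 416 per arm remain. For independent mothers,

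power = Φ(d / √[(0.0475 + 0.0862) / n] − 1.960),

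which gives about 80% at 513 and 71% at 416. That fall has nothing to do with trainers, so 71% is the right baseline for what follows.

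**Step 3. Add trainer correlation in the trained arm only.** The document gives none of the inputs. Assumed: 5, 10 or 20 trainers, ICC 0.005 to 0.05, 416 trained mothers followed, each mother with one trainer.

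- m = 416 / trainers, and DE = 1 + (m − 1) × ICC.
- Type I error of the plain chi-square: under the null the variance of the difference is inflated by (1 + DE) / 2, so α = 2 × [1 − Φ(1.960 / √((1 + DE) / 2))].
- Power of a test with the correct variance: Φ(d / √[(0.0475 + 0.0862 × DE) / 416] − 1.960).

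| Trainers | m | ICC | DE | Type I error | Power |
|---|---|---|---|---|---|
| 20 | 20.8 | 0.005 | 1.10 | 5.6% | 69% |
| 20 | 20.8 | 0.05 | 1.99 | 10.9% | 51% |
| 10 | 41.6 | 0.005 | 1.20 | 6.2% | 66% |
| 10 | 41.6 | 0.02 | 1.81 | 9.8% | 53% |
| 10 | 41.6 | 0.05 | 3.03 | 16.7% | 38% |
| 5 | 83.2 | 0.005 | 1.41 | 7.4% | 61% |
| 5 | 83.2 | 0.05 | 5.11 | 26.2% | 26% |

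With ICC 0, both columns return to 5% and 71%.

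**Step 4. Check with small groups.** If each trainer teaches 10 mothers and the ICC is 0.01, then DE = 1.09. At 520 per arm, type I error is 5.5% and power 78%, which is close to nominal. The result therefore depends heavily on how teaching is organised.

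**The case against.** A reader might infer that trained trainers deliver the whole intervention, and that the 5% error rate and 80% power therefore fail. The document does not support that. Training of Trainers is one item in an unclear list. The text does not say who gives the in-person teaching, whether mothers are taught in groups, or whether a mother keeps the same trainer over three sessions months apart. Video and online content is the same for everyone and need not cluster. The figure on implementation strategy is not available and may describe delivery. All of this stands, and it is why the effect can only be given as a range.

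Three further objections have force.

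- **Type I error.** If training changes nothing for any mother, differences in teaching quality cannot create correlation, and the error stays at 5% by that route. The inflated figures need trainer effects that vary around a zero mean, some helping and some harming, or trainers tied to centres that differ.
- **Centres.** Several hospitals do not by themselves inflate type I error. If each holds both arms in similar proportions, ignoring centre tends to be conservative. It is a threat only if arms are unevenly spread over centres, which the article does not say. No figure above rests on centre.
- **Unseen documents.** Chi-square is described as exploring associations and, in the Abstract, as an example of the methods. A full protocol or analysis plan may add centre or trainer terms. This weakens the point about the test. It does not touch the published sample size, which contains no allowance.

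**Conclusion.** The point holds in conditional form. The sample size is an independent-observations calculation with a design effect of 1, and the only named test makes the same assumption, while one arm alone receives teaching that may cluster by trainer. If outcomes do correlate within trainer, the chi-square interval is too narrow and power is below the independent-mothers figure.

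The direction is clear but the size is not. Over the assumed range the consequence goes from minor (20 trainers, ICC 0.005) to serious (5 trainers, ICC 0.05). The type I figures also require trainer effects that average to zero. The power figures use normal quantiles, so a proper small-sample correction with few trainers would lower them further. It cannot be said from the document that the 5% and 80% are actually wrong because of clustering. The shortfall from 80% to 71% comes from the dropout allowance and should not be counted here.

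**What to change.** 1. Record centre for every mother, and trainer (and session group, if groups are used) for every trained mother. Do this from the start, because trainer identity is hard to reconstruct later.
2. For the comparison of arms, replace the plain chi-square with a logistic model adjusted for centre, with trainer-clustered standard errors and a small-sample correction. A trainer random effect in the trained arm only is an alternative if it can be fitted. With few trainers and an outcome of 5% to 10% it may be unstable, so name the fallback in advance.
3. In Sample size & sampling methodology, state that the power assumes no trainer clustering, or restate it for an assumed ICC and number of trainers. State also how the arms are distributed over centres.

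The cost is one or two identifier fields and some analysis wording, with a somewhat wider interval and a less favourable stated power. If the correlation proves close to zero, little is lost.

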#### Implementation phase

This Phase of the study employs a non-randomized intervention design to assess the impact of a targeted multimethod parental educational intervention on antenatal mothers. This phase seeks to provide valuable insights into the practical application and potential benefits of the neuro parenting program. A comparison is made between the intervention group, exposed to the neuro parenting program, and a control group receiving routine care without training sessions. The primary outcomes center around evaluating the percentage of mothers who suspect early childhood developmental disorders including true positive, false positive and false negative ratio. The confirmation of DD will be done using Bayley Scale for Infant Development IV. The study entails a meticulously structured follow-up period, with strategically defined time points to assess the program’s efficacy across critical stages of early development. Assessments will be conducted at birth, six months, and twelve months postpartum to monitor developmental trajectories. By demarcating these specific follow-up intervals, the study ensures a systematic framework for evaluating intervention outcomes, particularly the capacity of mothers to recognize neurodevelopmental indicators and suspect potential developmental disorders. This follow-up design is structured to capture the program’s lasting influence on maternal awareness and accuracy in identifying developmental milestones, offering a precise evaluation of the intervention’s long-term impact. Through targeted assessments, the study will measure both immediate and long-term effects on maternal ability to recognize early developmental cues, providing a focused understanding of the intervention’s effectiveness. Implementation strategies are illustrated in Fig. 1 and the timeline has been depicted in Table 1.

